**Figure 3 figure3:**
[figure not shown]
Flow diagram depicting the study schedule for the assessment of effectiveness of Ayurvedic intervention in the QOL of older adults through the cluster randomized controlled trial. ADR: adverse drug reaction; QOL: quality of life.

**Figure 4 figure4:**
[figure not shown]
CONSORT (Consolidated Standards of Reporting Trials) diagram depicting the enrollment, allocation, and follow-up visits for the assessment of QOL in older adults through the cluster randomized controlled trial. QOL: quality of life.

### Sample Size

A change of 9 points on the OPQOL-Brief was expected in the intervention group (*Ayush Rasayana* A and B) compared to 6 points in the control group. With an SD of 8 points and a 95% CI, a sample of 150 participants per group would be needed to achieve 90% power. The estimates for the intervention group and SD were based on the results of a previously published study [11]. Considering the design effect of 2 clusters in this randomized controlled trial and an attrition rate of 20%, a sample size of 360 participants per group was needed. The sample size of each center needed to be 20 in each of the 2 groups. Therefore, the total sample size for each group was calculated as 360 for 18 study centers, and for the 2 groups, the total sample size was 720 (360 × 2). Therefore, a total of 720 participants were intended to be enrolled in the study. Initially, the sample size was calculated for 18 centers, and later on, 1 center was withdrawn from the study and the remaining sample size was distributed to the other centers as per Table 2.

**Table 2 table2:** Sample size distribution at 17 study centers for the evaluation of Ayush Rasayana A and B in older adults.

Area and location of the center		Sample size, n

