### Statistical Analysis

After data collection, verification of its accuracy and limits will be done. The filtered data will be utilized for additional analysis and interpretation. Categorical variables (eg, bowel movement: regular or irregular) will be reported as number (percentage), and the analysis of the pretrial-posttrial outcome will be done by a McNemar chi-square test. Continuous variables (eg, score and laboratory parameter) will be analyzed by a 2-tailed paired *t* test or Wilcoxon test as per the distribution of data in the pretrial-posttrial situation. Categorical variables will be analyzed through a chi-square test in the between-group comparison. Continuous variables will be analyzed through a 2-tailed unpaired *t* test or Mann Whitney *U* test in the between-group comparison. The assessment parameters assigned in more than 2 follow-ups will be analyzed using the r-ANOVA, Friedman test, or Cochran *Q* test. Continuous data with normal distribution will be represented as mean (SD), and data without normal distribution will be represented as median (IQR). The 5% level of significance will be used throughout the analysis. The SPSS (version 26.0l IBM Corp) software will be used to conduct the analysis.

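### The 20% attrition allowance was applied as ×1.2 instead of ÷0.80, so 360 per group does not follow from the plan's own inputs, and the design effect is worded as a count of clusters

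*Protocol article*

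**What the plan says.** All the inputs but one are in the Sample Size section of the protocol article.

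- Effect: "A change of 9 points on the OPQOL-Brief was expected in the intervention group", "compared to 6 points in the control group", a difference of 3 points.
- Variability and confidence: "With an SD of 8 points and a 95% CI".
- Individual-level result: "a sample of 150 participants per group would be needed to achieve 90% power".
- Clustering: "Considering the design effect of 2 clusters in this randomized controlled trial".
- Attrition and final size: "an attrition rate of 20%, a sample size of 360 participants per group was needed".

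The 360 is laid out as 20 participants per group at each of 18 centers. The section then reports that "later on, 1 center was withdrawn from the study". Table 2 keeps the total of 720 by raising some clusters from 20 to 22. That leaves 17 centers and 34 clusters, one cluster per arm at each center.

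The Statistical Analysis section gives the error rate: "The 5% level of significance will be used throughout the analysis". It describes its t tests as 2-tailed. The Abstract reports 686 of 720 participants (95.3%) completing.

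**The concern.** Two steps lead from 150 to 360, and each has a fault on the page.

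The first is the attrition step. An allowance for 20% loss should leave the required number after 20% of those enrolled have gone. Adding 20% to the required number does not do that, because the loss is taken from the larger enrolled number.

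The second is the design effect. It is a variance inflation factor, 1 + (m − 1) × ICC, set by the cluster size m and the intracluster correlation. It is not a number of clusters. The article's wording ties it to two clusters, perhaps because two were allocated at each center, while the trial as a whole has 34.

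The stake is how the result is read. Recruitment and follow-up are finished, but results are not yet published, and this paragraph is likely to be carried into the results paper. A null finding would then be read against 90% power at 20% loss, which the paragraph's own inputs do not quite give.

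**Working it through.** **Inputs.** Difference 3 points (9 − 6), SD 8, two-sided 5%, power 90%, design effect 2 (read from the arithmetic), attrition 20%, 360 per group, 17 clusters per arm. The 95% confidence level is read as two-sided 5%; a one-sided test would give 122, which does not match the article.

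**1. Reproduce 150.**
n = 2 × (1.960 + 1.2816)² × 8² / 3² = 149.4, rounded up to 150 per group. This agrees with the article.

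**2. Design effect.**
150 × 2 = 300 evaluable per group.

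**3. Attrition.**
- As printed: 300 × 1.20 = 360. The stated figure is matched exactly, by this route only.
- As needed: 300 / 0.80 = 375 per group, 750 in total. That is 15 per group, or 4.2%, more than 360.
- Loss at which 360 still leaves 300: 1 − 300/360 = 16.7%.

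**4. Power at the planned 20% loss, design effect held at 2.**
360 × 0.80 = 288 evaluable; effective n = 288 / 2 = 144 per group.
Expected test statistic = 3 / √(2 × 64 / 144) = 3.18.
- Normal approximation: 88.9%.
- Noncentral t with 2 × 17 − 2 = 32 df: 87.0%.

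These two figures should be read apart. With the full 300 evaluable (effective n 150) the same formulas give 90.1% (normal) and 88.3% (32 df). The attrition slip therefore costs about 1.2 to 1.3 points on either basis. The rest of the gap between 90% and 87% comes from using cluster degrees of freedom.

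**5. Power at the reported retention, design effect 2.**
686 / 2 = 343 per arm (equal split assumed); effective n = 343 / 2 = 171.5.
Expected test statistic = 3 / √(2 × 64 / 171.5) = 3.47.
- Normal approximation: 93.5%.
- t with 32 df: 92.0%.

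The Results section prints 760 enrolled beside the same 95.3%. Since 686/720 = 95.3% and 686/760 = 90.3%, 720 is used here. The power figure depends on the 686 and not on which denominator is right.

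**6. What a design effect of 2 implies.**
ICC = (2 − 1) / (m − 1). At m = 20 this is 1/19 = 0.053; at m = 16 (20 less 20%) it is 1/15 = 0.067.

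**7. Sensitivity to the ICC (an assumption, since none is given).** 17 clusters per arm, 288 evaluable, so m = 288/17 = 16.9; normal approximation:

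| ICC | Design effect | Effective n per group | Power |
|---|---|---|---|
| 0.02 | 1.32 | 218.4 | 97.5% |
| 0.05 | 1.80 | 160.3 | 91.9% |
| 0.10 | 2.59 | 111.0 | 79.8% |

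Using t with 32 df lowers these by roughly 1 to 2.5 points.

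**The case against.** The strongest reply is that the slip hardly matters. It costs about one point of power at the planned loss, and actual loss was 4.7%, well under the 16.7% that 360 can absorb. On a design effect of 2 the trial as run has more than 90% power. That stands, and it sets the size of this point. It does not make 360 the right result for the inputs printed beside it.

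A second reply is that holding the design effect at 2 after 20% loss is harsh, because smaller clusters have a smaller design effect. If the ICC is fixed at 1/19, then at m = 16.9 the design effect is 1 + 15.9/19 = 1.84 and the effective n is 288/1.84 = 156.6. Power is then 91.3% (normal) or 89.6% (32 df). This is correct as far as it goes. But the article states a factor of 2 and no ICC, so the 87–89% is what its own stated factor gives, and it should be labelled as conditional on that factor.

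A third reply is that the design-effect phrase is only loose wording, and that a condensed article may leave the ICC to the full protocol. The arithmetic supports this: a factor of 2 was used, and no cluster count entered it wrongly. The absence of an ICC is therefore not a fault in itself. The printed phrase still describes the quantity incorrectly.

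A reader might go further and infer that the design fails to deliver 90% power, or that the trial was underpowered. The documents do not support that. At an ICC near 0.05 power is about 90% or above even at 20% loss, and it falls clearly below only at ICCs such as 0.10, which nothing in the article suggests. Without a stated ICC, power is unverified, not shown to be deficient. A lower figure based on a center-paired analysis with 16 df would not be fair either, because the article does not state such an analysis.

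**Conclusion.** The point holds as a small arithmetic error and a wording error. From the article's own inputs, 20% attrition requires 375 per group and not 360. With 360 and 20% loss, power at a design effect of 2 is 88.9% by the normal approximation or 87.0% with 32 df. Only about 1.2 to 1.3 points of the shortfall are due to the attrition step. At the reported 686 completers, power at a design effect of 2 is about 92–93%, so the error has no demonstrated consequence for the trial as run.

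These figures assume a two-sided 5% test, a 3-point difference, SD 8, a design effect of exactly 2, 17 equal clusters per arm for the t figures, and an equal split of completers between arms. The ICC of about 0.05 is implied by a factor of 2 at 20 per cluster; it is not stated in the article.

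**What to change.** Keep 720. Enrolling 375 per group is no longer possible, because follow-up is complete. In the Sample Size paragraph, and wherever it is carried into the results paper:

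1. State either that 360 per group allows for up to 16.7% attrition from 300 evaluable, or that at 20% attrition and a design effect of 2 power is about 87–89%.
2. Add that at 686 completers, with equal arms assumed, power is about 92–93% at a design effect of 2.
3. Replace the reference to two clusters with *a design effect (variance inflation factor) of 2*, and note that at 20 per cluster this corresponds to an ICC of about 0.05. If the full protocol holds the ICC that was actually used, cite that value instead.

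The cost is the rewording of one paragraph and a slightly lower power figure at the planned attrition. No participants, data or analyses change.

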**Scheduled Tribe–dominated areas (8 centers and 16 clusters)**		
	Agartala	44^a^
	Gwalior	44^a^
	Patna	44^a^
	Chennai	44^a^
	Vijayawada	44^a^
	Jammu	40^b^
	Guwahati	40^b^
	Bangalore	40^b^
	Total	340
**Scheduled Caste–dominated areas (9 centers and 18 clusters)**		
	Cheruthuruthy	44^a^
	Bangalore	44^a^
	Nagpur	44^a^
	Gangtok	44^a^
	Ahmadabad	44^a^
	Bhubaneswar	40^b^
	Kolkata	40^b^
	Mumbai	40^b^
	Jammu	40^b^
	Total	380

^a^Clusters with a sample size of 22 in each group.

^b^Clusters with a sample size of 20 in each group.

### Randomization

The preexisting groups of the population in the selected areas were identified and divided into 5 clusters at each center as per the geographical demarcation. Of these, 2 clusters were randomly assigned to either the intervention or control group by a cluster randomization chart, prepared using a computer-generated sequence by the statistics department of the CCRAS. The participants were recruited through door-to-door surveys, outreach outpatient departments, and medical camps from the selected clusters by the investigators at each study center using voluntary sampling.

### Blinding

The study was open label in execution; therefore, blinding was not done.

### Data Collection

The investigators complied with the requirements for all assessments and data collection. The demographic data, clinical history, details of concomitant medications, and outcome parameters were documented. During follow-ups, the occurrence of any symptom and need for any rescue medication were recorded**.** Data capture for this study was planned to be in both hard copies of the case report form (CRF) and an electronic format. All source documentation supporting entries into the CRFs was maintained, and data were checked for consistency, omissions, and any apparent discrepancies. After the completion of the study, the data will be analyzed and published without disclosing the personal identification of the participants.

### Concomitant and Rescue Medication

The drug or medications administered to treat the participant’s additional illness were noted by the study investigators. The participant continued any concomitant therapy for diabetes mellitus, hypertension, or any other disease during the study, which were not specifically excluded. Any medical emergency would have been relieved with the administration of any rescue drug. This would have been properly documented in the CRF.

### Statistical Analysis

After data collection, verification of its accuracy and limits will be done. The filtered data will be utilized for additional analysis and interpretation. Categorical variables (eg, bowel movement: regular or irregular) will be reported as number (percentage), and the analysis of the pretrial-posttrial outcome will be done by a McNemar chi-square test. Continuous variables (eg, score and laboratory parameter) will be analyzed by a 2-tailed paired *t* test or Wilcoxon test as per the distribution of data in the pretrial-posttrial situation. Categorical variables will be analyzed through a chi-square test in the between-group comparison. Continuous variables will be analyzed through a 2-tailed unpaired *t* test or Mann Whitney *U* test in the between-group comparison. The assessment parameters assigned in more than 2 follow-ups will be analyzed using the r-ANOVA, Friedman test, or Cochran *Q* test. Continuous data with normal distribution will be represented as mean (SD), and data without normal distribution will be represented as median (IQR). The 5% level of significance will be used throughout the analysis. The SPSS (version 26.0l IBM Corp) software will be used to conduct the analysis.

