## Methods

### Study Design

The study was an open-label, multicenter, parallel-group, cluster randomized controlled trial conducted in 2 groups with an allocation ratio of 1:1.

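### The named between-group and repeated-measures tests ignore the cluster randomisation that the sample size was doubled for; if the planned design effect of 2 acts at cluster level, the nominal 5% test errs about 16.6% of the time

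*Protocol article*

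**What the plan says.** **Design.** Protocol article, Study Design: a "cluster randomized controlled trial conducted in 2 groups with an allocation ratio of 1:1". The Randomization section says that each centre's area was divided into 5 clusters and continues: "Of these, 2 clusters were randomly assigned to either the intervention or control group by a cluster randomization chart". Table 2 counts 16 + 18 = 34 clusters over 17 centres, and its footnotes give 22 or 20 participants in each group. That is one cluster per arm at every centre.

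**Sample size.** The Sample Size section states "A change of 9 points on the OPQOL-Brief was expected in the intervention group", against 6 points in the control group, and "With an SD of 8 points and a 95% CI, a sample of 150 participants per group would be needed to achieve 90% power". It then inflates: "Considering the design effect of 2 clusters in this randomized controlled trial", together with 20% attrition, gives 360 per group.

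**Analysis.** The Statistical Analysis section says "Categorical variables will be analyzed through a chi-square test in the between-group comparison. Continuous variables will be analyzed through a 2-tailed unpaired" t test or Mann-Whitney U test. Parameters assessed at more than two follow-ups go to r-ANOVA, the Friedman test or Cochran Q. The 5% level applies throughout. The section names no mixed model, GEE, robust variance or cluster-level summary, and no cluster or centre term.

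**The concern.** A test between arms has to use the variation between the units that were randomised. Here those units are 34 clusters. Each named between-group test treats the roughly 700 participants as independent, so its standard error leaves out any variation between clusters within an arm. The Sample Size section assumes that this variation doubles the variance, while the Statistical Analysis section proceeds as if it were absent. The two sections cannot both be right.

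This touches the primary outcome and every secondary comparison between arms. OPQOL-Brief is measured at baseline and on days 34, 62 and 90, so the repeated-measures line may be the one that analyses it, and that line has the same gap. What is at stake is a false-positive rate above the declared 5%, and confidence intervals that are too narrow, in a trial whose Conclusion looks ahead to treatment protocols and public health programmes.

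**Working it through.** **Inputs from the article:** difference 9 - 6 = 3 points; SD 8; two-sided 5%; power 90%; design effect (DE) 2; attrition 20%; 34 clusters; 720 planned and 686 completing.

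**1. Reproduce the plan's figures.** n per group = 2 × (1.96 + 1.2816)² × 8² / 3² = 149.4, rounded up to 150, as stated. Then 150 × 2 × 1.2 = 360, as stated. The phrase about the design effect is loosely worded, but this arithmetic shows that the factor used was 2.

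**2. ICC implied by DE = 2.** Mean cluster size m = 720/34 = 21.2. From DE = 1 + (m - 1) × ICC, ICC = 1/20.2 = about 0.050 (0.048 at m = 22, 0.053 at m = 20).

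**3. Error of a test that ignores clustering.** The true variance of the contrast is DE times the one used, so type I error = 2 × (1 - Φ(1.96/√DE)). With DE = 2, 1.96/1.414 = 1.386, which gives 16.6%. Coverage of a nominal 95% interval is 100 - 16.6 = 83.4%, and its width is 1/√2 = 0.71 of the correct width.

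| DE | Type I error |
|---|---|
| 1.2 | 7.4% |
| 1.5 | 11.0% |
| 2 | 16.6% |
| 2.5 | 21.5% |
| 3 | 25.8% |

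**4. Allow for both arms being at each centre.** The article gives neither an ICC nor its split between centre and cluster, so the split is an assumption and is varied here. Simulation: 17 centres, two clusters each of 22 (10 centres) or 20 (7 centres), no true effect, 20,000 runs per row.

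| ICC at centre level | ICC at cluster level | Individual-level test | Paired t test on 17 centre differences |
|---|---|---|---|
| 0 | 0.05 | 16.9% | 5.0% |
| 0.025 | 0.025 | 10.6% | 5.1% |
| 0.04 | 0.01 | 6.6% | 4.7% |
| 0.05 | 0 | 4.5% | 5.1% |
| 0.05 | 0.05 | 16.0% | 4.9% |

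The first four rows hold the total ICC at 0.05. The last doubles it.

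**5. Would a real effect survive correction?** Assume that the 686 completers split equally, 343 per group. The individual-level SE for 3 points is 8 × √(2/343) = 0.611, so z is about 3/0.611 = 4.9. Divided by √2 this is about 3.5, above the critical t of 2.12 on 16 df. By contrast, an individual-level result needs |z| above 1.96 × √2 = 2.77 (p below about 0.006) to remain significant at DE = 2, or above 2.12 × √2 = 3.00 (p below about 0.003) with 16 df.

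**6. Power of a valid test.** For completers m = 686/34 = 20.2. With ICC 0.052 (DE = 2 at that size), the variance of a cluster mean is 64 × (0.052 + 0.948/20.2) = about 6.34. The SE of the mean of 17 differences is √(2 × 6.34/17) = 0.864, so the non-centrality is 3/0.864 = 3.47. On 16 df this gives power of about 90%.

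**The case against.** The strongest case is about size. A design effect of 2 is a planning value, not an observation, and no ICC is given. Because every centre holds one cluster of each arm, correlation shared within a centre cancels in the contrast. Omitting the centre term makes the test conservative, which works against the effect of omitting the cluster term. If nearly all correlation is at centre level, the individual-level test is close to nominal (4.5% in the simulation). This stands, and it means that 16.6% has to be stated as conditional. A reader might take 16-17% as the trial's actual false-positive rate; the article does not support that.

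A reader might also infer that no positive result could be trusted. That goes too far: step 5 shows that an effect of the planned size would probably remain significant after correction. The results at risk are the borderline ones.

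A third objection is that a condensed article leaves such detail to a full protocol or an analysis plan that is not shown. That would answer a silence, but the article is not silent. It names the between-group tests, and they do not fit the design that it describes.

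**Conclusion.** The point holds in conditional form. The analysis as written conflicts with the cluster design and with the article's own design effect. If the planned design effect of 2 acts at cluster level (ICC about 0.05), the nominal 5% test has a true error of about 16.6% and a nominal 95% interval covers about 83%. With the split between centre and cluster unknown, the error at a total ICC near 0.05 runs from about nominal, through 10.6% with equal shares, to about 17%. It exceeds that if the cluster-level ICC is larger: DE = 3 gives 25.8%. These figures were worked out for the unpaired comparison of means. The Mann-Whitney, chi-square and repeated-measures tests share the omission but were not simulated.

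Uncertainty about the split does not rescue the stated tests. They hold 5% only if there is almost no cluster-level correlation, which is not what the sample size assumed. The paired cluster-level test held 4.7-5.1% under every split tried. This should be corrected before analysis.

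**What to change.** Replace the between-group and repeated-measures tests with an analysis by randomised unit. Date the change and fix it before the arms are compared: the trial is open label, follow-up ended in April 2024, and the article describes the data analysis as still to be completed.

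- **OPQOL-Brief and other continuous outcomes:** a linear mixed model with arm, baseline score and centre as fixed effects, a random cluster effect, and small-sample degrees of freedom (about 16 for arm). For the repeated visits add visit, arm-by-visit and a participant-level term or covariance.
- **Simpler valid alternative:** a paired t test on the 17 within-centre differences in cluster means of change. It is not identical to the model, since it differs in baseline adjustment and in the weighting of unequal clusters.
- **Binary outcomes:** a paired cluster-level comparison of proportions, or a GLMM or GEE with small-sample correction.
- **Reporting:** give the observed ICC.

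The cost is a dated change to the analysis text. No new data are needed, and SPSS, the software already named, fits linear mixed models. The interval will usually be wider, but correct, and power for 3 points stays about 90% under the planned assumptions.

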### Outcome Measures

The primary outcome measure was the change in the QOL of the older adults, assessed by Older People’s Quality of Life Questionnaire-Brief (OPQOL-BRIEF) at baseline and on the 34th day, 62nd day, and 90th day. The secondary outcome measures included any change in the Katz Index of Activities of Daily Living, Pittsburgh Sleep Quality Index (PSQI), Five Times Sit-to-Stand Test, shoulder joint mobility, hematological and biochemical parameters (complete blood count, liver function test, and renal function test), and the occurrence of treatment-emergent adverse events during the study period at the baseline and on the 90th day.

The OPQOL-Brief is a short measurement for QOL developed from the OPQOL-35 questionnaire [13]. It contains 13 questions scored from 1 (strongly agree) to 5 (strongly disagree) based on the response from the participant. The total score is calculated after reverse coding the positive items so that higher scores represent higher QOL. The Katz Index of Activities of Daily Living is a dichotomous scoring tool used for measuring independence in older adults. It measures the functional independence of a person, assessing self-care tasks under 6 domains: bathing, dressing, toileting, transferring, continence, and feeding [14]. The PSQI is a widely used scale comprising a combination of Likert-type and open-ended questions in 7 components: subjective sleep quality, sleep latency, sleep duration, sleep efficiency, sleep disturbance, use of sleep medication, and daytime dysfunction—each with scores ranging from 0 to 3. Higher PSQI scores indicate more acute sleep disturbances, thus a lower quality of sleep [15]. The Five Times Sit-to-Stand Test is a measure used to assess functional independence and mobility. It evaluates the time required to stand as rapidly as possible from a sitting posture for 5 repetitions; the shorter the time taken by the person, the better the functional condition [16]. The change in shoulder joint mobility is assessed through simple physical maneuvers for the active range of movements: active abduction, and external and internal rotations. Each maneuver is assessed separately by 3-point scales for the range of mobility (fully able=3, partially able=2, and unable=1) and pain on movement (no pain=1, some pain=2, and lots of pain=3) on both sides. A sum score for all 3 maneuvers on each side is estimated for the range of movement and pain separately.

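### The plan does not fix which test, contrast or visit decides the primary OPQOL-Brief outcome

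*Protocol article*

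**What the plan says.** Outcome Measures in the Protocol article defines the primary outcome as change in OPQOL-Brief, assessed "at baseline and on the 34th day, 62nd day, and 90th day". The secondary outcomes are listed for baseline and day 90 only. No visit is singled out as primary.

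Statistical Analysis then gives three sets of tests that could reach this outcome:

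- Pre-post: "Continuous variables (eg, score and laboratory parameter) will be analyzed by a 2-tailed paired" t test, or Wilcoxon.
- Between groups: "Continuous variables will be analyzed through a 2-tailed unpaired" t test, or Mann-Whitney U.
- Repeated measures: "The assessment parameters assigned in more than 2 follow-ups will be analyzed using the r-ANOVA, Friedman test, or Cochran" Q test.

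On error control the section says: "The 5% level of significance will be used throughout the analysis".

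Sample Size plans on a comparison of arms. "A change of 9 points on the OPQOL-Brief was expected in the intervention group", "compared to 6 points in the control group". It continues: "With an SD of 8 points and a 95% CI, a sample of 150 participants per group would be needed to achieve 90% power".

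**The concern.** The repeated-measures sentence is the only rule tied to the visit pattern of the primary outcome, and it does not state a comparison of arms. Friedman compares time points within one set of participants. A repeated-measures ANOVA yields a time effect, and it yields an arm contrast only if a group factor and a group-by-time term are included. The sentence mentions neither. The unpaired test does compare arms, but it is a general rule for continuous variables. The section does not tie it to OPQOL-Brief, attach it to a visit, or say how it ranks against the repeated-measures rule.

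The trial's main conclusion is at stake. The protocol itself expects controls on ancillary care alone to gain 6 points, so a change over time says almost nothing about the product. The trial is also open label with a questionnaire as its primary outcome, which makes improvement in both arms a realistic prospect. If the unpaired test is used instead, it can be run at three visits, each at the full 5%.

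**Working it through.** **1. Which rule covers the primary outcome.** OPQOL-Brief has three follow-ups after baseline, and every secondary outcome is listed for baseline and day 90. The repeated-measures rule therefore captures the primary outcome and no other listed outcome. Cochran Q is for binary data and cannot apply to a total of 13 five-point items. For this outcome the options under the rule are r-ANOVA and Friedman.

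**2. Which contrast the trial was sized on.** Inputs from Sample Size: difference 9 − 6 = 3 points, SD 8, two-sided 5%, 90% power.

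n per group = 2 × (z₀.₉₇₅ + z₀.₉₀)² × SD² / difference² = 2 × 3.2415² × 64 / 9 = 149.4, rounded up to 150.

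This reproduces the stated figure (power at 150 per group: 90.1%). The figure comes from a two-arm contrast of change, which no sentence in Statistical Analysis names as the primary test.

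**3. What a within-arm test shows if the product adds nothing.** Suppose both arms gain the 6 points expected of controls. Take the stated SD of 8 as the SD of change, as the sample size formula does. Then t = 6 / (8 / √n):

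| n in the arm | Source | t |
|---|---|---|
| 360 | planned per group | 14.2 |
| 288 | 360 × 0.8, after 20% attrition | 12.7 |
| 150 | base sample size | 9.2 |

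This does not depend on the SD being right. At an assumed SD of 16 and n = 150, t is 4.6 and the chance of p < 0.05 is still 99.6%. Nor does clustering rescue it: with the planned design effect of 2, the 288 shrinks to an effective 144, and t = 6 / (8 / √144) = 9.0.

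A null simulation agrees (1,000 runs; 17 clusters of 21 per arm; both arms gaining an assumed 2, 4 and then 6 points; assumed between-visit correlation of change 0.5; no clustering effect). Within one arm, Friedman and the paired t test at day 90 were each significant in 100% of runs. The between-arm t test at day 90 was significant in 5.9%, close to its nominal level.

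**4. What three between-arm tests do.** With the arms compared at days 34, 62 and 90, each at 5%, the chance of at least one false positive is 1 − 0.95³ = 14.3% if the tests are independent. The documents give no between-visit correlation, so a range is assumed:

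| Assumed correlation | Familywise error |
|---|---|
| 0.3 | 13.5% |
| 0.5 | 12.5% |
| 0.7 | 10.9% |
| 0.9 | 8.3% |

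The simulation in step 3 gave 13.2% for significance at any of the three visits.

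**The case against.** Four points can fairly be made for the plan.

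First, it does contain a comparison of arms. The sentence just before the repeated-measures rule gives an unpaired t or Mann-Whitney test for continuous variables, and OPQOL-Brief is a total score. Nothing says that the later rule replaces this one. This stands, and it rules out the claim that the primary outcome has no between-arm test available.

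Second, r-ANOVA can carry a group factor and a group-by-time term. This also stands: the method is under-specified, which is not the same as lacking an arm contrast.

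Third, a reader might infer that the plan will declare effectiveness from improvement within the intervention arm. The document does not say so. Sample Size is built on 9 against 6 points, and Expected Findings describes the purpose as evaluating the intervention against control. The intent is between-arm.

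Fourth, the primary visit, model terms and multiplicity rules are often left to an analysis plan, which is not shown here. As an objection to missing detail this would succeed. It does not succeed here, because the article states a rule that reaches the primary outcome, and that rule does not match the contrast on which the trial was sized.

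The multiplicity figures also presume three separate visit tests, which the plan leaves open but does not prescribe.

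**Conclusion.** The point holds in this form: Statistical Analysis does not settle which test, which contrast or which visit decides the primary outcome, and so it leaves room for a time-effect or pre-post result to be read as effectiveness.

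If the decision rested on a within-arm test, significance would be practically certain with no product effect. That rests on the protocol's own 6-point control gain and SD of 8, and it survives a doubling of the SD. If it rested on any of three between-arm visit tests at 5%, the error would be about 8% to 13.5% for assumed correlations of 0.9 to 0.3.

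A reader might also want to add the effect of ignoring clusters, since none of the named tests allows for them. In the same simulation with a design effect of 2 ignored, the false-positive rate was 16.3% for day 90 alone and 28.7% for any visit. Most of the excess at a single visit has nothing to do with the choice of visit. It is a separate defect and should not be counted in the size of this one.

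**What to change.** Before any comparison by arm, add a dated paragraph that names one primary analysis: the between-arm difference in OPQOL-Brief at day 90, adjusted for baseline OPQOL-Brief, from a mixed or cluster-level model that accounts for the clusters, two-sided 5%. Day 90 is the end of the treatment period and the visit shared with the secondary outcomes.

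Do not use Friedman for the primary outcome. If a repeated-measures model is kept, state its group and group-by-time terms and take the day-90 between-arm contrast from it. Treat days 34 and 62, and all within-arm pre-post tests, as supportive, with no claim of effectiveness from them.

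Because the trial is open label and follow-up is complete, the paragraph should state that no outcome had been compared by arm when it was written, if that is the case. The article describes the analysis as still to come. The cost is one paragraph and slightly more analysis work, with no new data.
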